## 1. Title of the clinical trial

*The Effectiveness of Chuna Manual Therapy Based on Radiographic Malposition Diagnosis in Patients with Non-acute Low Back Pain (a randomized controlled, two-arm, parallel study, assessor-blind)*

---

## 3. Sponsor of the clinical trial

- Sponsor: Ministry of Health and Welfare
- Implementing agency: Korea Health Industry Development Institute

## 4. Objectives and background of the clinical trial

### 4.1 Objectives

This clinical trial aims to explore the therapeutic effects of Chuna manual medicine based on radiographic malposition diagnosis in patients with non-acute low back pain.

---

### 4.2 Background

#### 4.2.1 Low back pain

- Low back pain is one of the most common musculoskeletal disorders worldwide; 70–80% of people experience it at least once in their lifetime.
- In many countries, low back pain is a leading cause of disability and medical expenditure, imposing a great socioeconomic burden.
- In particular, **non-acute** (subacute or chronic) low back pain often shows a recurrent or persistent course and tends to become chronic, requiring long-term management.

#### 4.2.2 Usual non-invasive treatments for low back pain

- Recent clinical practice guidelines on non-invasive treatment of low back pain recommend various options such as pharmacologic therapy, psychological therapy, physical therapy, exercise, manual therapy, and patient education.
- Among these, **spinal manual therapy** has been recommended with low-moderate levels of evidence as a treatment option for acute, subacute, and chronic low back pain.

#### 4.2.3 Chuna manual therapy

- **Chuna manual therapy (CMT)** is a Korean manual treatment performed by Korean medicine doctors that includes techniques aimed at restoring balance between anatomical structures and their functions.
- Since 2019, Chuna manual therapy has been covered by the Korean National Health Insurance for musculoskeletal disorders, and various studies have verified its efficacy and safety.
- Diagnostic procedures performed before Chuna treatment can broadly be divided into:
  1. **Manual palpation-based diagnosis**, and
  2. **Instrument-assisted diagnosis** using imaging devices (radiological imaging) or posture-analysis devices.
- However, there is still a serious lack of data on:
  - The objectivity of each diagnostic method,
  - Inter- and intra-rater reliability, and
  - Analyses of treatment outcomes according to diagnostic results.

#### 4.2.4 Previous studies on imaging-based diagnostic methods for Chuna medicine

##### (1) Domestic clinical studies

##### (a) Overview

- To date, diagnostic methods for Chuna based on radiological data include:
  - Establishing a diagnostic system,
  - Developing an AI-based diagnostic program using vertebral landmarks, and

- Clinical studies assessing concordance of Chuna diagnoses and applying AI programs.
- Chuna radiographic diagnosis performed on the basis of a standard operating procedure (SOP) developed through expert consensus has been shown to demonstrate **higher inter-rater agreement** than palpation-based diagnostic methods.

## (b) A Summary Study on the Composition of a Diagnostic Method for Chuna Based on Plain X-ray Images

1. **Stage 1 – Establishment of a diagnostic system (2011–2014)**
  - *Literature review on nomenclature systems for spinal malposition*
    - Classified and presented nomenclature systems for Chuna-based spinal malposition.
  - *Development of a diagnostic method for Chuna medicine using plain radiography of the spine.*
    - Performed Chuna malposition diagnosis by comprehensively considering bony structures visible on radiographs.
2. **Stage 2 – Development of an AI-assisted diagnostic program (2015–2017)**
  - *Development of an AI program based on vertebral body landmarks on plain radiographs*
    - Constructed an AI model that identifies vertebral landmarks on lumbar radiographs and outputs malposition patterns corresponding to Chuna diagnostic categories.
3. **Stage 3 – Clinical studies on diagnostic concordance and application of AI (2017–2020)**
  - *Study on concordance between different diagnostic methods (palpation, radiographic diagnosis, AI program)*
    - Reported that radiographic diagnosis showed higher inter-rater reliability than palpation-based diagnosis, and that the AI program achieved a level of diagnostic agreement similar to that of Chuna experts.
  - *Application of the AI program in clinical practice*
    - Demonstrated the feasibility of applying the AI-based diagnostic program in real-world clinical settings.

## (2) Overseas research related to AI-based vertebral position analysis

- Overseas studies on AI programs for vertebral position analysis have mainly focused on **evaluation of scoliosis** (e.g., Cobb angle measurement) rather than on assessing vertebral alignment and malposition from the perspective of manual medicine.
- Studies that diagnose vertebral malposition patterns in a way directly applicable to manual medicine techniques are largely lacking.

### (3) Key previous work

#### 1. Chuna diagnostic method using plain radiography (2014)

- Presented a new diagnostic approach using plain radiographs as a way to compensate for limitations of manual Chuna diagnosis and to ensure objectivity and reproducibility.
- Conducted Chuna malposition diagnosis by comprehensively evaluating bony structures on plain films.
- Based on these findings, standard operating procedures (SOPs) for classification of malposition patterns and corresponding Chuna treatment methods were developed.

#### 2. Development and validation of AI-assisted vertebral malposition diagnosis

- Used vertebral body landmarks extracted from lumbar radiographs to train AI models that output malposition categories used in Chuna medicine.
- Reported that the AI-based method shows acceptable agreement with expert Chuna diagnoses and has potential for use as a clinical decision-support tool.
- Jin-hyun Lee, et al. Comparison of Concordance between Chuna Manual Therapy Diagnostic Methods (Palpation, X-ray, Artificial Intelligence Program) in Lumbar Spine: An Exploratory, Cross-Sectional Clinical Study. *Diagnostics (Basel)*. 2022 Nov 8;12(11):2732. doi: 10.3390/diagnostics12112732.)

### Rationale and strengths of this study

#### ○ Need for a study evaluating the effectiveness of applying Chuna interventions based on radiological assessment

- To date, previous studies on radiological assessment in Chuna medicine have mainly taken the form of retrospective studies, such as conceptual overviews, establishment of diagnostic landmarks, and evaluation of inter-observer agreement between different diagnostic methods. However, no study has actually evaluated, in real clinical practice, the effectiveness of a Chuna treatment approach that is guided by radiological data-based Chuna diagnostic methods.
- Therefore, a clinical trial is needed in which standardized Chuna treatment methods are applied according to displacement (malposition) patterns assessed on imaging, in order to verify their clinical effectiveness.

#### ○ Application of interventions with demonstrated efficacy and safety

- By adopting a pragmatic study design, we set a usual-care control group according to previous studies and clinical guidelines, and apply Chuna therapy to patients with conditions for which safety and effectiveness have already

been demonstrated in prior research. This allows the clinical trial to be conducted efficiently in a real-world clinical context.

## ○ Provision of relevant evidence for clinical practice in Korean medicine

- Chuna imaging diagnosis based on radiological data, together with extraction of imaging biomarkers, can serve as an objective basis for comparing and evaluating the effects of Chuna treatment before and after the intervention. This will enable the accumulation of more rational and objective clinical data for future Chuna-related clinical research.
- The development of biomarkers and diagnostic techniques for rational Chuna diagnosis can be used as foundational research to support future insurance coverage (reimbursement) of Chuna diagnostic procedures.

## 5. Description of the interventions

### 5.1 Radiograph-based Chuna diagnostic method used in this clinical trial

#### 5.1.1 Radiographic acquisition method

For evaluation of lumbar spinal segment alignment, we will use the radiographic positions that were employed in previous studies that verified the reproducibility of lumbar alignment measurements. These radiographic procedures follow the standardized protocols of Chiropractic Biophysics (CBP) and were designed to increase the reproducibility and reliability of radiographic acquisition.

#### (1) Anteroposterior (AP) view

- The participant stands barefoot, and the midline of the pelvis is aligned with the central beam of the X-ray unit.
- The pelvic mid-sagittal plane is aligned to the central beam, and the buttocks are centered relative to the detector.
- The participant is instructed to nod the head forward and backward twice and then assume a neutral head position.
- The participant then closes the eyes, opens them, and looks straight ahead naturally.
- Abnormal pelvic posture (for example, lateral tilt) is not artificially corrected, so that the image reflects the participant's habitual alignment.
- The X-ray beam is centered at the L3 level, with a standard source-to-image distance of 101.6 cm (40 inches), and is generally kept horizontal.

#### (2) Lateral view

- The shoulders and pelvis are positioned perpendicular to the X-ray beam.
- The participant moves the head twice to find a neutral position.

- The arms are crossed in front of the chest to minimize changes in pelvic or thoracic posture.
- Abnormal lumbar posture is not corrected, so that the natural alignment is reflected.
- The X-ray beam is directed toward the L4 level from a distance of 101.6 cm (40 inches).
- These positions are designed to allow accurate measurement of pelvic axis, lumbar curvature, and segmental inclination of the lumbar vertebrae.

### 5.1.2 Chuna diagnostic method for spinal malposition

- Using DICOM files of the acquired lumbar radiographs, we apply the digital markers proposed in previous studies and derive the flexion, lateral bending, and rotation angles for each vertebral body.
- A DICOM labeling program (Dicomlabel, Korea Institute of Oriental Medicine, Daejeon, Korea) is used to generate the segmental angles.

#### (1) Generation of digital markers

- **Lateral view**
  - For each lumbar vertebral body, the anterior and posterior end points of the superior endplate are connected to form the superior line, and the anterior and posterior end points of the inferior endplate are connected to form the inferior line.
  - To diagnose malposition of L5, reference points on the sacrum are also required. Therefore, digital markers are created using two endplate end points on S1, the line connecting them, and additional sacral landmarks as specified in the standard operating procedure.
- **AP view**
  - For each lumbar vertebral body, the left and right end points of the superior endplate are connected to form the superior line, and the left and right end points of the inferior endplate are connected to form the inferior line.
  - In addition, the most medial points of the bilateral pedicles are identified as additional landmarks.
  - For diagnosis of L5 malposition, digital markers are generated using the left and right end points of the superior surface of S1 and the line connecting them, the most lateral points of the sacral ala, and the midpoint of the S2 spinous process.

#### (2) Determination of malposition based on angular values

- Based on the angles derived by the program, the presence or absence of malposition is determined.

- Using the previously derived threshold values for malposition diagnosis (cut-off angles), segments with angles equal to or exceeding the threshold are classified as having Chuna-defined vertebral malposition (for example, if the flexion angle of L1 is 3°, it is diagnosed as a flexion malposition).
- For rotational malposition of L5, there is no separate segment below L5. Therefore, the value is used only when the left-right distance difference between the sacral ala and the S2 tubercle falls within the normal range specified by the program; otherwise, the value is recorded in the case report form but treated as missing in malposition diagnosis and statistical analysis.
- The reference threshold angles for each lumbar vertebral body are as follows

|                     | Vertebral body |       |       |       |       |
|---------------------|----------------|-------|-------|-------|-------|
|                     | L1             | L2    | L3    | L4    | L5    |
| Flexion(° )         | 0.64           | 3.56  | 5.29  | 8.90  | 8.53  |
| Extension(° )       | 10.46          | 14.95 | 17.61 | 20.76 | 24.47 |
| Lateral bending(° ) | 2.21           | 2.10  | 1.92  | 2.06  | 2.31  |
| Rotation(° )        | 9.49           | 5.19  | 4.59  | 5.87  | 7.13  |

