### 5.2.2 Chuna manual therapy (applied only in the Chuna treatment group)

#### (1) Application of Chuna therapy according to radiograph–based diagnostic results

- In the Chuna treatment group, Chuna manual therapy is performed based on the Chuna diagnostic results derived from the plain radiographs.
- Treatment is provided twice per week for 4 weeks (approximately 15 minutes per session), for a total of 8 sessions.
- According to the diagnostic results, the standardized operating procedures (SOPs) specified in the protocol are used to select the treatment method.
- Based on the classification of Chuna diagnostic results into simple and complex malposition patterns, Chuna treatment methods specified in the SOP are applied to the corresponding vertebral levels.
- When more than one corrective technique is presented in the SOP for a given malposition, the practitioner may choose the most appropriate technique according to clinical judgement.
- If, in the clinical judgement of the practitioner, additional Chuna therapy is required for regions other than the lumbar spine (for example, the pelvis), such techniques may be applied, and these procedures will be recorded in the case report form.
- However, for the lumbar spine itself, no Chuna techniques other than those specified in the SOP may be applied.

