## 3) Treatment visits (Visits 3–10; both groups)

(1) Chuna + usual care group (Group I; Visits 3–10)

- Starting immediately after the baseline visit, participants receive treatment **twice per week for 4 weeks**, for a total of **8 sessions** according to the allocated intervention (usual care + Chuna).

(2) Usual care-only group (Group II; Visits 3–10)

- Starting immediately after the baseline visit, participants receive **usual care only** twice per week for 4 weeks (8 sessions).

(3) Assessments at each treatment visit (both groups)

- Before treatment at each visit, the following items are checked:
  - Occurrence of adverse events since the previous visit.
  - Vital signs: sitting blood pressure, pulse rate, body temperature (measured after at least 5 minutes in the sitting position without abrupt postural changes).

---

**4) Assessment visits** (same for Groups I and II – Visits 2, 10, and 11)

(1) All participants who pass screening will visit the outpatient clinic at baseline, at the end of the treatment period (4 weeks after baseline), and 8 weeks after completion of all treatments (12 weeks after baseline) to undergo the following assessments.

(2) Vital signs

(3) Assessment of subjective symptoms and function

- Primary and secondary efficacy outcomes are assessed using questionnaires on pain intensity and function: NRS, ODI, EQ-5D-5L, and RMDQ.

(4) Physical examination

- Lumbar range of motion (ROM):  
Flexion, extension, lateral flexion (right and left), rotation (right and left).

(5) Imaging evaluation

- Standardized lumbar spine AP and lateral standing radiographs (L-spine AP & lateral standing view) are obtained.
- Based on the acquired images, vertebral-level relative angles (flexion, extension, lateral bending, rotation) and Chuna malposition diagnosis results are derived using a DICOM labeling program and compared across time points.

(Note: No separate imaging assessment is performed at Visit 2; the imaging evaluation at Visit 2 is replaced by the screening radiographs obtained at Visit 1.)

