### 3. Imaging evaluation

- At baseline (screening radiographs), week 4, and week 12, **L-spine AP and lateral standing radiographs** are obtained according to the standardized imaging protocol.
- Using a DICOM labeling program developed by the Korea Institute of Oriental Medicine, the following are calculated for each lumbar vertebral level:

- Relative angles for **flexion, extension, lateral bending, and rotation**,
- **Chuna malposition diagnosis results** based on the predefined cut-off values.
- These imaging parameters are used as secondary or exploratory outcomes to investigate changes in spinal alignment and their association with clinical improvement.

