## 15. Statistical analysis

The analysis sets used for the evaluation of data obtained in this clinical trial will be defined as follows:

- **Intention-to-treat (ITT) set**
  - The ITT set consists of **all participants who were randomized and received the trial intervention at least once**.
- **Full analysis (FA) set / Full analysis set (FAS)**
  - The FAS consists of all participants who:
    - were randomized, and
    - received the trial intervention at least once, and
    - have **at least one post-baseline efficacy assessment**.
  - The FAS follows the ITT principle and will be used as the **primary analysis set for efficacy**.
- **Per-protocol (PP) set**
  - The PP set includes participants who meet **all** of the following conditions:
    1. Fully satisfy the **inclusion and exclusion criteria**.

2. Have completed at least the **minimum predefined number of treatment sessions** (patients who received **5 or more** of the total 8 planned treatment sessions).
  3. Patients whose treatment was completed because they **met the predefined criteria for treatment completion due to symptom improvement**.
- **Safety analysis (SA) set**
    - The safety analysis set consists of all participants who were randomized and received the trial intervention **at least once**, and for whom **at least one safety assessment** was performed.
    - The SA set will be used for **all safety analyses**.
- 

In this clinical trial, the general principle for statistical analysis is as follows:

- All statistical tests will be **two-sided**, with a **significance level of  $\alpha = 0.05$** .
- Efficacy analyses will primarily be performed using the **full analysis set (FAS)**, with the **PP set** used as a **supplementary analysis**.
- Safety analyses will be performed in the **ITT (SA) set**, i.e., all randomized participants who received at least one treatment.

For missing data:

- For **continuous efficacy variables** in the FAS, missing values will be imputed using the **Last Observation Carried Forward (LOCF)** method, replacing missing values with the most recent available value prior to the missing time point.
- For all other variables, missing data will **not** be imputed, and analyses will be performed using the observed data as they are.

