### b. Analysis of secondary efficacy outcomes

Secondary efficacy outcomes will be analyzed using methods consistent with those for the primary efficacy outcome, focusing on changes from baseline (week 0) to the end of treatment (week 4) and follow-up (week 12).

- ① **Change in NRS for leg pain (radiating pain)**
  - The change in NRS for radiating leg pain from baseline to weeks 4 and 12 will be analyzed.
- ② **Evaluation of subjective pain intensity and quality of life related to low back pain**
  - Changes in the following outcomes from baseline to week 4 and week 12 will be analyzed:
    - ODI,
    - EQ-5D,
    - RMDQ.

For these continuous variables, within-group tests and between-group comparisons will be performed in the same manner as for the primary outcome (paired t-test or Wilcoxon signed-rank test for within-group changes; ANCOVA or appropriate nonparametric tests for between-group comparisons, as appropriate).

---

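### L5 rotation readings that the protocol itself voids are, on a literal reading, filled by LOCF, so a void week-4 reading is analysed as a change of exactly zero

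*Protocol*

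**What the plan says.** **Validity rule (Protocol section 5.1.2 (2)).** The protocol singles out one measurement: "For rotational malposition of L5, there is no separate segment below L5". The L5 rotation angle therefore counts only if the left-right difference in distance between sacral ala and S2 lies in the labelling program's normal range. For a reading outside that range, "otherwise, the value is recorded in the case report form but treated as missing in malposition diagnosis and statistical analysis". No such check applies to L1–L4, or to L5 flexion, extension or lateral bending.

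**Missing-data rule (section 15).** Continuous efficacy variables in the full analysis set are imputed by LOCF, "replacing missing values with the most recent available value prior to the missing time point". All other variables are left unimputed, "and analyses will be performed using the observed data as they are". Neither sentence mentions values voided by the validity check.

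**Status of the angles (section 14.1, Imaging evaluation).** Relative angles, rotation included, and malposition results are derived for each lumbar level at baseline, week 4 and week 12. Of their role the protocol says: "These imaging parameters are used as secondary or exploratory outcomes to investigate changes in spinal alignment and their association with clinical improvement". The assessment-visit text in section 8 adds that angles and diagnoses "are derived using a DICOM labeling program and compared across time points".

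**The concern.** LOCF is usually meant for a participant who was not seen. Here the participant attended and was filmed, and one reading failed a quality check. The validity rule rejects the reading because it cannot be trusted. The imputation rule then puts an older reading in its place as if it had been taken on the new film.

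Two things follow on a literal reading:

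- A void week-4 angle becomes a change of exactly zero, whatever happened to the segment.
- Two outcomes from one measurement are handled differently. The angle is continuous and is filled. The malposition diagnosis is categorical and stays missing.

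At stake is the L5 rotation comparison and any association between L5 rotation change and clinical improvement, which section 14.1 names as a purpose of the imaging outcomes. Artificial zeros distort both.

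**Working it through.** **Inputs from the protocol.** The L5 rotation cut-off is 7.13° (section 5.1.2 (2)). The visits are baseline, week 4 and week 12. The LOCF rule is in section 15. The protocol states no figure on this point that could be reproduced.

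**Assumptions, not in the protocol.** The share of void readings v is taken as 10% to 40% per visit. Voiding is random and baseline readings are valid. The effect sizes below are illustrative.

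**One record.** Suppose L5 rotation truly falls from 9° to 6°.

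- Both readings valid: change = 6 − 9 = −3°. The angle moves from above to below 7.13°, so the malposition resolves.
- Week-4 reading void: LOCF enters 9°, so change = 9 − 9 = 0°. The week-4 malposition diagnosis is missing.

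**Week 4, equal void rates.** A share (1 − v) contributes its true change and a share v contributes zero. With true group difference D4:

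expected LOCF difference = (1 − v) × D4

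| v | Factor | D4 = −2.0° | D4 = 0.50 SD |
|---|---|---|---|
| 10% | 0.9 | −1.8° | 0.45 |
| 20% | 0.8 | −1.6° | 0.40 |
| 30% | 0.7 | −1.4° | 0.35 |
| 40% | 0.6 | −1.2° | 0.30 |

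A simulated ANCOVA of change on group and baseline (400,000 per arm, baseline-to-follow-up correlation 0.6) gave 0.449, 0.398, 0.349 and 0.299 SD, matching the last column. Using valid readings only, it returned 0.497 to 0.499 SD.

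**Week 12, equal void rates.** A void week-12 reading takes the week-4 value if that is valid, and the baseline value only if week 4 is void too. With void shares v4 and v12, independent of each other:

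expected LOCF difference = (1 − v12) × D12 + v12 × (1 − v4) × D4

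- Week 12 only void (v12 = 30%, v4 = 0), sustained effect 0.5/0.5: 0.7 × 0.5 + 0.3 × 0.5 = 0.50. No bias.
- The same, waning effect 0.5/0.2: 0.7 × 0.2 + 0.3 × 0.5 = 0.29 against a true 0.20. Inflated.
- 30% void at both visits, sustained: 0.7 × 0.5 + 0.3 × 0.7 × 0.5 = 0.455 against 0.50. Shrunk.
- 30% void at both visits, growing effect 0.2/0.5: 0.7 × 0.5 + 0.3 × 0.7 × 0.2 = 0.392 against 0.50. Shrunk.

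The simulation gave 0.499, 0.289, 0.455 and 0.391 for these four cases.

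**Week 4, unequal void rates.** Let control improve by 0.5 SD and Chuna by 1.0 SD, a true difference of 0.50.

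- 10% void in Chuna, 30% in control: 0.9 × 1.0 − 0.7 × 0.5 = 0.55. Inflated.
- 30% void in Chuna, 10% in control: 0.7 × 1.0 − 0.9 × 0.5 = 0.25. Shrunk.

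**Sample size.** It rests on low back pain NRS alone: 2 × (1.96 + 0.84)² / 0.96² = 17.01, so 18 per group; 18 / 0.8 = 22.5, so 23. This reproduces the protocol's figures, and L5 rotation plays no part in it.

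**The case against.** The strongest objection is that LOCF on imaging angles is inferred. Section 15 names no imaging analysis. Its secondary analyses cover leg-pain NRS and the list introduced by "Changes in the following outcomes from baseline to week 4 and week 12 will be analyzed", which is ODI, EQ-5D and RMDQ. Its exploratory analyses cover procedures, early termination and rescue medication. One can also argue that the specific validity rule prevails over the general missing-data sentence, so that void values simply stay out. How a derived radiographic variable is analysed is often left to the SAP, which is not at hand.

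Much of this stands, and it lowers the priority. It does not remove the point. The LOCF sentence covers continuous efficacy variables without exception, the angles sit under efficacy evaluation, and the validity rule uses the very status, missing, that triggers imputation. A programmer following the text could reasonably fill these values.

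A reader might also infer more than the protocol supports:

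- *Any L5 alignment effect shrinks.* This holds at week 4 with similar void rates. A waning effect at week 12, or more void readings in the control arm, inflates it.
- *The film is unusable.* Only L5 rotation is voided. The other L5 angles remain.
- *The number of malpositions falls artificially.* The protocol defines no participant-level count and does not score a void diagnosis as absent.
- *Void rates will differ by arm.* Section 5.2.2 (1) says that in Group I, where "additional Chuna therapy is required for regions other than the lumbar spine (for example, the pelvis), such techniques may be applied". Nothing in the protocol shows that this alters the ala-S2 difference or the share of void readings. Differential voiding is possible but unsupported.

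A void baseline reading is a separate matter. It follows from the validity rule alone and is not cured by changing LOCF.

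**Conclusion.** The point holds in limited form. Read literally, the two rules turn a void week-4 L5 rotation reading with a valid baseline into a change of exactly zero, while the matching diagnosis stays missing. Under equal, random void rates and valid baselines, the week-4 difference is cut to 0.9 to 0.6 of its value for an assumed void rate of 10% to 40%. The true rate is unknown, so the real loss could be smaller or larger. At week 12, or with unequal rates, even the direction is not fixed.

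One direction at one level is affected, out of 20 cells in the threshold table (five levels by four directions), in outcomes labelled secondary or exploratory, in a pilot of 46. The primary NRS analysis is untouched. This is a low-priority clarification, worth making because it is cheap.

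**What to change.** Add to the missing-data rules in section 15 that L5 rotation values voided under section 5.1.2 (2) are not imputed by LOCF, and that L5 rotation is analysed from the valid readings as observed. In section 14.1, Imaging evaluation, state that L5 rotational malposition status is compared between two visits only where it is assessable on both films. Report the number of void L5 rotation values by arm and visit, so that a reader can see how much was lost and whether the arms differ.

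The cost is two or three sentences and a small programming change. Fewer participants will contribute to the L5 rotation comparison. Analysis of valid readings recovers the true effect only if voiding is unrelated to the angle. That is why the void counts should be shown.
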